(vii) Program beneficiaries and non-beneficiaries: To study and compare beneficiaries and eligible non-beneficiaries of the program in the community in terms of: socio-demographic characteristics, utilization of antenatal services, birth attendance, delivery outcome, birth weight, receipt of post natal care, immunization of the child and costs of care incurred. Reasons for participation/non participation and choice of place of delivery will be explored. Predictors of non-participation will also be studied.

(viii) Equity in access to facilities (geographic): To estimate the influence of distance to facilities on place of delivery in comparison to other determinants of delivery service use.

(ix) Role of community health workers in program uptake: To study the role played by the ASHA (accredited social health activist) and the traditional birth attendants (TBA) in the antenatal, delivery and postnatal periods of program mothers. Also to explore among ASHAs their motives for participation and long term professional aspirations within the NRHM. The dynamic between various community level workers, the TBA, the ASHA and the female health worker will be explored. Concerns on the potential duplication of roles between the latter two will be explored among policy makers.

**Table 2 T2:** Summary of objectives and proposed methods at the implementation level

**Study level**	**Objectives**	**Proposed methods**
Provincial (Policy)	To study program utilization trends	Secondary data analysis - complete times series, Document reviews, Key person interviews with policy makers, program managers and private sector representatives, Stakeholder discussions
	To ascertain the influence of changes in ANC service utilization and institutional deliveries on maternal and neonatal outcomes	
	To study trends in private sector participation	
	Explore the motivations for participation/non participation with the private sector in CY program	
	To understand the exclusion of the private sector in the JSY program	
	Explore experience of private provider in JSY	
	Comparison of emergency care transportation systems	
	Cost effectiveness of the programs and the emergency transportation models	
District (Facility)	List and classify all facilities performing deliveries according to their EmOC functionality	Facility Survey, Observations of normal deliveries, Register and case record review, Case vignettes to study provider competence, In depth exit interviews with mothers

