	Survey and describe facilities conducting deliveries	
	Assess the quality of care administered in study facilities	
	Study outcomes (type of delivery, maternal mortality and morbidity, foetal outcomes) among program beneficiaries and non-beneficiaries in study facilities	
	Experiences of public and private sector physicians of the programs (in terms of task load, shifting of tasks, human resources required, monetary transactions with the program)	
Community	Identify program beneficiaries and non-beneficiaries.	Questionnaires, In-depth interviews, Focus group discussion, Spatial methods (GIS) to study distance
	Study differences between background characteristics, geographic access to EmOC, outcomes (maternal), type of health service utilization in pregnancy (and delivery), use of emergency obstetric transportation services and expenditures during delivery	
	Identify predictors for program uptake	
	Compare infant health status and health service utilization between users and non-users.	
	Among users, study perceived quality of care at facility	
	Explore motives and barriers for participation/non-participation among eligible beneficiaries and non-beneficiaries	
	Understand the working dynamic for the community health workers(ASHA, TBA & female health workers)and their role in the program	

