For the observations, content analysis will be used to conceptualize and classify events, behaviors and actions to obtain a rich understanding of quality of care and explanation of how women experience care at facilities [16]. Basic descriptive statistics will be calculated for key indicators from the record and register review. With regard to provider competence, descriptive analysis will identify competence areas that require strengthening. The data will be analyzed using inferential statistics to compare scores between levels of facilities and qualification and experience of providers. The data from exit interviews will be analyzed to describe use of evidence based practices by level of facility. Qualitative data derived from the in-depth interviews with mothers will be analyzed using the thematic Framework approach [17]. The obstetric referrals, indications for referral and details of referral-transport, costs, distance, and time will be described by the level of facility using mean, standard deviation and tests of significance. The referral pathways of the maternal deaths will be mapped on GIS and buffer analyzed. The buffer analysis will be used to study referring facility locations with regard to transfer time to CEmOC facilities.

3. Community level (mothers in the study villages):

At the community level we will collect primary data from recently delivered mothers to compare outcomes between eligible beneficiaries and non-beneficiaries (objective vii) for each of the programs. A cross-sectional study will be conducted with women residing in the selected study villages who delivered in the last year. JSY program participation is defined as an institutional delivery in any public health facility. Program non participation is defined as a home or private facility delivery. CY program participation is defined as a below poverty line (BPL) or tribal mother who delivers in a CY approved facility. Program non participation is defined as BPL or tribal mother who delivers outside of a CY approved facility.

Stratified systematic random sample will be used to select the study villages in each district. The districts will first be stratified by blocks (administrative units) and then the villages in each block will be classified into two strata based on the size of the population. Villages will be randomly selected from each strata based on the population proportion. Given the different design of each program, the sample sizes will vary in each province.

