There will be three points of data collection; (i) when the woman delivers, (ii) 15 days and (iii) 28 days post-delivery. The ASHA will administer a simple symptom based checklist to all mothers regardless of place of delivery to ascertain maternal morbidity, complications associated with the pregnancy and delivery, at the three time points. To ensure quality data collection, a physician will administer a second checklist to 5% of all mothers which will be compared to the data collected by the ASHA.

Socio-demographic details, history of previous pregnancies, receipt of comprehensive maternal health care (antenatal, intrapartum and post natal care), place of delivery, delivery type, birth weight, immunization of the child, indirect and direct costs associated with delivery, program participation and maternal and neonatal outcomes will be elicited post-delivery in the mother’s home by a trained research assistant. In addition, reasons for participation/non-participation in the program, reasons for their choice of facility and barriers (if any) to access of care will be collected. Data will also be collected on household amenities and assets. This will help create an indicator to assist in quantifying the degree of income related inequalities and how it influences the inequities in access to care. In the event of a maternal death, the head of the household will be requested to provide the information.

Propensity score matching will be used to select a comparison group from the sample of non-participants closest in terms of observable characteristics to a sample of program participants. Comparisons of the outcome variables described above between the two groups (users and non-users) will be studied. Reasons for participation/non participation will be described. In a separate hierarchical model, the predictors of non-participation will be studied in each program. Costs incurred will be compared by place of delivery.

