The assessment of *impact* will be made from secondary and primary data. One measure of impact will be the influence of the programs on the final outcome i.e. maternal mortality. This will involve the construction of statistical estimates from secondary data sources as detailed on page 9. A second assessment of impact will be to study differences in outcomes among eligible beneficiaries and non-beneficiaries. While a randomized experimental study would have been the most robust design (balancing confounders between users and non-users), this is not feasible for these specific large programs as they have been rolled out nationwide/statewide. Hence, there are no non-program groups from which a random sample can be drawn. Given that the two programs are implemented completely across the provinces under study and so preclude a randomized design for evaluation, we will generate the comparison groups (counterfactual) using matched comparisons. In this evaluation, propensity score matching [24] will be used to select a comparison group from the sample of non-users closest in terms of observable characteristics to a sample of program participants.

In addition to performance and impact of the two programs, a *cost utility* analysis of each of the programs from a payer (state) and patient perspective will be done. There have been no previous economic analyses of these programs.

In summary, this paper describes a comprehensive evaluation protocol for two innovative demand side financing programs to promote maternal health in India. The protocol comprises an assessment of the performance and impact of the programs as well an economic analysis. The implementation of the protocol will generate evidence to facilitate decision making among policy makers and program managers who currently work with or are planning similar programs in different contexts. The evaluation also aims to fill existing evidence gaps in the scientific literature on the performance and impact of large scale demand side financing programs for maternal health. The results from the studies in this protocol will help support the design of efficient demand side financing programs in the future.

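### Birth attendance is compared between users and non-users who are themselves defined by place of delivery, so a large gap appears even if the program changed nothing

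*Protocol article*

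**What the plan says.** The article fixes four things that have to be read together.

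- **Groups, JSY** (Data collection methods, Community level): "JSY program participation is defined as an institutional delivery in any public health facility", and "Program non participation is defined as a home or private facility delivery".
- **Groups, CY** (same section): "CY program participation is defined as a below poverty line (BPL) or tribal mother who delivers in a CY approved facility", and "Program non participation is defined as BPL or tribal mother who delivers outside of a CY approved facility".
- **Compared variables** (Background, objective vii): beneficiaries and eligible non-beneficiaries are compared on several items, among them "utilization of antenatal services, birth attendance, delivery outcome, birth weight, receipt of post natal care".
- **Analysis and reading**: propensity score matching picks the non-participants most similar to participants in observable characteristics, and then "Comparisons of the outcome variables described above between the two groups (users and non-users) will be studied" (Community level). The Discussion says: "A second assessment of impact will be to study differences in outcomes among eligible beneficiaries and non-beneficiaries". It treats the matched non-users as the counterfactual.

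No sentence excludes variables that follow from the group definition.

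**The concern.** Who attends a birth depends mainly on where it takes place. Under these definitions every user delivered in a facility, and every woman who delivered at home is a non-user. A user/non-user difference in attendance therefore mostly restates the definition of a user.

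This is not ordinary confounding. Even with perfect balance on background characteristics, all matched users remain facility births, and home births can occur only among the matched non-users.

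The Background says the programs are meant to lower financial barriers to skilled attendance, so this contrast bears on their intended mechanism. A large gap would look like success. It could not separate a program that brought women into facilities from one that paid for women who would have delivered there anyway.

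**Working it through.** The article gives no sample size, effect size or expected difference for this comparison, so there is no figure of its own to reproduce. The check asks what gap the definitions produce when the true program effect is zero.

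**Inputs**
- I, institutional delivery: 0.47 in Madhya Pradesh and 0.56 in Gujarat (Table 3). For Gujarat the state-wide rate is assumed to hold for BPL and tribal mothers. A value of 0.80 is added as an assumed sensitivity case.
- s, share of facility births in participating facilities (assumed): 0.60-0.90 in Madhya Pradesh, 0.20-0.80 in Gujarat, 0.20-0.90 in the sensitivity case.
- f, attendance at facility births: 0.98 (assumed). h, attendance at home births: 0.05-0.30 (assumed).

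**Formulae (each woman's place of birth is the same with or without the program)**
- Home share among non-users: H = (1 − I) / [(1 − I) + I(1 − s)]
- Attendance among users: f
- Attendance among non-users: (1 − H)f + Hh
- Gap: H(f − h)

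**Results**

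| Setting | s, h | H | Non-user attendance | Gap |
|---|---|---|---|---|
| MP, smallest | 0.60, 0.30 | 0.53/0.718 = 0.738 | 47.8% | 0.738 × 0.68 = 50 points |
| MP, largest | 0.90, 0.05 | 0.53/0.577 = 0.919 | 12.6% | 0.919 × 0.93 = 85 points |
| Gujarat, smallest | 0.20, 0.30 | 0.44/0.888 = 0.495 | 64.3% | 0.495 × 0.68 = 34 points |
| Gujarat, largest | 0.80, 0.05 | 0.44/0.552 = 0.797 | 23.9% | 0.797 × 0.93 = 74 points |
| I = 0.80, smallest | 0.20, 0.30 | 0.20/0.840 = 0.238 | 81.8% | 0.238 × 0.68 = 16 points |
| I = 0.80, largest | 0.90, 0.05 | 0.20/0.280 = 0.714 | 31.6% | 0.714 × 0.93 = 66 points |

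User attendance is 98% in every row, and the true program effect is 0 points in every row.

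**Does matching help?** A simulation with zero program effect used 1,000 women per run and 500 runs. One background characteristic drove facility birth, and users were matched 1:1 to the nearest non-user on it. Attendance was set to 100% in facilities and to 15% or 30% at home. The mean matched gap was 74 and 47 points in two Madhya Pradesh settings, and 39 and 32 points in two Gujarat settings. Matching trimmed the home share among non-users only a little. In the first Madhya Pradesh setting it went from (1 − 0.469)/(1 − 0.422) = 0.919 to 0.874. That reduction is the confounding that matching can address; the rest comes from the definition.

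**The case against.** The best defence is that the article never ties attendance to an impact claim in a single sentence. Objective vii is a list of things to study and compare, and it opens with socio-demographic characteristics. Table 2 lists maternal outcomes and type of service use as separate items. The Discussion speaks of differences in outcomes without naming attendance. The choice of variables for the matched analysis could sit in a fuller document.

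Part of this stands: the link is made by joining three places. But the group definitions, the compared variable, the matched comparison and the impact reading are all stated, and nothing limits attendance to description. A fuller document could not make attendance independent of place of birth while these definitions hold.

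Three stronger readings are tempting, and the text does not support them.

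- *Place of delivery and program participation are declared outcomes.* They appear in a list of everything the research assistant collects, which also holds socio-demographic details and names maternal and neonatal outcomes separately. Place of delivery matters here only if the words "Comparisons of the outcome variables described above between the two groups (users and non-users) will be studied" are taken to cover it. Participation is plainly the exposure.
- *The contrast contains nothing the program could change.* JSY non-users include private-facility births, and CY non-users include eligible births in any other facility. Both I and s could respond to a program. The sound statement is narrower: the contrast does not identify a program effect on attendance.
- *A false-positive rate can be quoted.* The article names no test or significance level for this comparison, so rejection rates would describe an analysis it does not specify.

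**Conclusion.** The point holds for birth attendance, and for any other variable that place of delivery fixes. With zero program effect, the plan as written gives an attendance gap of about 50-85 points in Madhya Pradesh and 34-74 points in Gujarat. At 80% institutional delivery the gap is about 16-66 points. Matching on background characteristics does not remove it.

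The direction follows from the definitions alone, provided attendance is higher in facilities than at home. The size rests on figures the article does not give: the participating share of facility births, attendance in facilities and at home, and the use of the state-wide rate for eligible women in Gujarat. The ranges should be read as orders of magnitude.

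Birth weight, immunization, and maternal and neonatal outcomes are not caught by this circularity. They face ordinary confounding, which is what matching is meant to address.

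**What to change.** 1. In objective vii and the Community level methods, state that birth attendance, and any other variable fixed by place of delivery, is excluded from the matched impact comparison. Name place of delivery explicitly, so that the phrase about outcome variables cannot be read to include it.
2. Report these variables descriptively, as the distribution of place of delivery and attendant among all eligible sampled mothers in each province.
3. Draw statements about program influence on institutional delivery from the district time series of objective i, which already contains it. That series does not list birth attendance, so it cannot supply a skilled-attendance estimate. Make no impact claim on skilled attendance from the user/non-user contrast.
4. Keep the matched comparison for outcomes the grouping rule does not fix, such as birth weight, immunization, and maternal and neonatal outcomes.

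The cost is a change of wording and one descriptive table, with no new data. The downside is the loss of one favourable-looking contrast.

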With regard to the JSY program in MP, to explore the reasons for the decision to subsequently reduce the role of the private sector in the program. Also to explore among selected erstwhile participating private facilities, their experience with JSY and their perception on the state decision to exclude them from the scheme.

With regard to the CY program, to explore experiences and motivations among selected private providers currently participating in the program, reasons for non-participation among a sample of those who were eligible but never participated and those who participated initially but have since left the program.

(iii) Emergency transportation for obstetric care: To study two different emergency obstetric transportation models utilized in each of the programs with regards to coverage, equity in access, current utilization, and cost of the service. Further, to explore among a group of mothers their experience of gaining access to and using the transportation.

(iv) Cost-effectiveness of the Programs: To develop and apply a model for assessment of the utility of the two maternal health programs and to perform a sensitivity analysis by testing alternative assumptions for a cost utility analysis.

2. Facility Level (public and private facilities):

(v) Facility Survey: To list all facilities in the study districts offering obstetric care and classify them as non-EmOC, basic or comprehensive emergency obstetric care (BEmOC or CEmOC) facilities. Further, to study the characteristics of these facilities with regard to ownership, accessibility, bed strength, human resources, training, referral communications and processes, availability of equipment, drugs and supplies and infection control procedures.

(vi) Quality of Care: To study in EmOC facilities the quality of care through direct observation of normal deliveries, a review of case records and registers and assessments of provider competence. Further to study experiences and perceptions of quality of care of mothers who delivered under the respective programs, and to study key procedures they experienced. In cases of mothers who were referred into facilities, referral indications and transportation details will be studied.

3. Community level (mothers in sampled study villages):

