At the facility level we will collect primary data on the types of facilities that are administering obstetric care under the programs (objective v), and the quality of care received (objective vi). These facilities will be visited to study maternal health outcomes. Both quantitative and qualitative methods will be utilized to achieve these objectives.

An initial list of all public and private facilities in the study districts will be obtained from government records. The list will be verified by site visits. Snowballing will then be utilized to identify any missing private facilities where obstetric care is provided. A modified Averting Maternal Death and Disability (AMDD) survey [12] will be administered to each facility by a member of the research team and the performance of EmOC functions will be ascertained by interviewing key staff. The facilities will be classified with reference to standards based on the UN and WHO definitions [13] as non-EmOC, Basic Emergency Obstetric Care (BEmOC) or Comprehensive Emergency Obstetric Care (CEmOC). The availability level of EmOC services will be ascertained with reference to the population; the number of CEmOC, BEmOC and non-EmOC facilities in the public and private sector and in the rural and urban areas will be calculated.

A cross-sectional survey will provide additional information on how the facilities function under the respective programs as well as aspects of quality of care provided. The assessment will include variables on infrastructure, accessibility, human resources, functional equipment, accessibility to drugs and supplies, referral communications and processes, infection control procedures and service statistics. This survey will provide the current operating state of the facilities. Descriptive statistics will be calculated for the areas mentioned above. These will be compared between public and private facilities and between the two programs.

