The facilities identified in objective v will be mapped onto a Geographic Information System (GIS) (objective viii). Digitized GIS maps of the selected districts in both provinces will be created. The map will have basic layers of district and block boundaries, road and rail networks, and settlements. Global Positioning System (GPS) co-ordinates will be taken for all facilities and added to the map as a separate layer. The location of the mothers who participated or did not participate in the program (objective vii) will be added as an additional layer. Distance from the mothers’ village to the selected health center will be calculated from the GIS. The association between distance from a facility and program use will be studied. Level of care offered at the facility will also be used as a predictor in the model for choice of place of delivery. Suitable GIS software along with standard statistical software will be used. A regression model will be developed using the background predictors of place of delivery (maternal characteristics, socioeconomic situation) as well as distance to the nearest facility.

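### Nearest-facility distance comes from a map that stops at the study-district border: it is too long for some border villages, and attenuates the distance effect to the extent that women cross

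*Protocol article*

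**What the plan says.** Four statements in the protocol article fix how distance is measured.

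- **Facility list.** Objective v (Background) is "To list all facilities in the study districts offering obstetric care and classify them as non-EmOC, basic or comprehensive emergency obstetric care". Under Data collection methods, Facility Level: "An initial list of all public and private facilities in the study districts will be obtained from government records". The list is then checked by site visits, and "Snowballing will then be utilized to identify any missing private facilities where obstetric care is provided".
- **Map.** Under Data collection methods, Community level: "The facilities identified in objective v will be mapped onto a Geographic Information System (GIS) (objective viii". On its extent: "Digitized GIS maps of the selected districts in both provinces will be created".
- **Exposure.** The regression for place of delivery uses background predictors "as well as distance to the nearest facility". A second measure comes from the same map: "Distance from the mothers’ village to the selected health center will be calculated from the GIS". The facility's level of care also enters the model for choice of place of delivery.
- **Villages and outcome.** "The districts will first be stratified by blocks (administrative units) and then the villages in each block will be classified into two strata". Border blocks are not excluded. The same section defines JSY participation as delivery in any public facility, and CY participation as delivery by an eligible mother in an approved facility. Neither definition has a district limit.

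The article mentions no facilities from neighbouring districts, no margin around the mapped districts and no check for border villages.

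**The concern.** The outcome and the exposure have different geographic limits. A delivery in the next district counts in the outcome, but the facility where it took place is not on the map from which distance is read.

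For a village whose true nearest facility is over the border, the plan returns the distance to a farther facility inside the district. If its mothers do use the nearer one, they behave like women living close to care while being coded as living far from it. That flattens the fitted relation between distance and place of delivery.

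Objective viii sets the influence of distance against other determinants of delivery service use. A flattened coefficient would understate distance in exactly that comparison.

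A second, narrower gap concerns a woman who delivered outside the district. Her chosen facility has no coordinates on the map and no surveyed level of care.

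**Working it through.** The article gives no facility count, district size, crossing rate or distance effect, so there is no stated figure to reproduce. The direction of the distance error follows from logic; the size can only be illustrated.

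**Step 1: direction.** For village v, let F be all facilities and D the mapped ones, with D a subset of F.

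- d_true(v) = minimum distance from v over F
- d_map(v) = minimum distance from v over D

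A minimum over a subset cannot be smaller, so d_map ≥ d_true. They are equal when the nearest facility is in D. Border villages whose nearest facility is inside the district are therefore measured correctly.

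**Step 2: a village-level test from the map alone.** Let b(v) be the straight-line distance from v to the edge of the mapped area. Every unmapped facility is at least b(v) away. If b(v) ≥ d_map(v), none can be nearer, and d_map(v) is exact (given a complete list inside the districts). Only villages with b(v) < d_map(v) can be wrong.

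**Step 3: size with free crossing.** Assumptions, none from the documents: square district of side 60, 80 or 100 km; 10, 30, 60 or 120 facilities expected per district, placed at random; equal density outside; 400 villages with 10 mothers each; true log-odds slope −0.10 per km; women use the nearest facility regardless of borders; 200 runs per setting. Results for the 80 km district:

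| Facilities | Villages with too long a distance | Same, within 5 km of border | Mean excess (km) | Slope, true distance | Slope, mapped distance | Ratio |
|---|---|---|---|---|---|---|
| 10 | 19.8% | 46.4% | 9.2 | −0.100 | −0.063 | 0.627 |
| 30 | 11.4% | 37.0% | 4.9 | −0.100 | −0.075 | 0.748 |
| 60 | 8.2% | 30.6% | 3.5 | −0.099 | −0.078 | 0.788 |
| 120 | 5.7% | 23.2% | 2.4 | −0.102 | −0.088 | 0.855 |

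Across all three district sizes, 5.7% to 20.2% of villages were affected, with a mean excess among them of 1.8 to 10.5 km. The ratio ran from 0.627 to 0.855, an attenuation of 1 − 0.855 = 14.5% to 1 − 0.627 = 37.3%. No mapped distance was too short in any run.

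**Step 4: dependence on crossing.** With 50 facilities per district, the ratio of fitted to true slope was:

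| Crossing | Ratio |
|---|---|
| All villages can cross | 0.78 |
| Half can cross | 0.89 |
| None cross | 1.01 |

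Without crossing, in-district distance is the relevant exposure and the bias vanishes.

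**Step 5: does the Step 2 check work?** Refitting without villages where b(v) < d_map(v) gave ratios of 0.97 to 1.02 in every setting run. It dropped 19% to 51% of villages, more where facilities are sparse.

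**The case against.** **Crossing is assumed.** The participation definitions are analysis rules and are no evidence on where women travel. Under Data collection methods, the free obstetric transport in Madhya Pradesh is contracted locally at district level, and CY operates only in Gujarat. Both suggest that some borders may be hard to cross. This stands: attenuation is conditional on crossing.

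**Facilities may be dense.** Table 3 implies 72.6/50 = 1.45 million people per district in Madhya Pradesh and 60.4/25 = 2.42 million in Gujarat, and objective v counts every facility offering obstetric care. Ten per district may be too few, which favours the lower end of the effect. This also stands, although the documents give no count. A reader might infer that distance to comprehensive emergency care suffers most, but objective viii does not state that exposure.

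**Women who crossed are not lost.** A reader might infer that they drop out of the analysis. Nearest-facility distance is measured from the village and exists for every mother, and place of delivery is asked at home. Only the distance to the selected facility and its surveyed level of care are unavailable. The article does not say how a missing level of care would be handled, so exclusion from the model is not established.

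**This is detail for the full protocol.** This does not stand. The article states the facility frame, the map extent and the exposure, and the error follows from those three choices. Snowballing does not cure it: it is described as finding missing private facilities, while JSY participation depends on public ones.

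**Conclusion.** The point holds in a limited form. As written, the plan can only overstate nearest-facility distance, and does so for villages whose true nearest facility lies across an unmapped border. To the extent that women cross, the distance effect in objective viii is attenuated; if they do not, it is unbiased.

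The simulated attenuation of about 14% to 37% rests on free crossing, random placement and equal facility density outside. It shows that the effect need not be trivial and is not an estimate for this study. The text does not say whether any study districts adjoin; a border between two mapped districts would cause no error.

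Two stronger readings are not supported. One is that the distance effect is biased whatever women do; Step 4 shows otherwise. The other is that border villages are typically the remote ones; nothing in the article says so.

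The issue touches one exposure in one of nine objectives, but it is the exposure which that objective is about, and the check is cheap.

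**What to change.** 1. **Border check.** Flag each village whose straight-line distance to the edge of the mapped area is shorter than its mapped nearest-facility distance. Do not count a border shared by two mapped study districts as an edge, and let nearest distance run across it. Repeat the place-of-delivery model without flagged villages and report both fits. This needs no new data. The price is precision: 19% to 51% of villages were dropped in the simulations. Flagged villages also tend to have the longer mapped distances, so the refit covers a narrower range.
2. **Selected-facility distance.** Have the home interview record which facility was used, and add the location of any out-of-district facility that mothers name. Its level of care would come from records and not from the survey, and should be marked as such.
3. **Extended layer.** Where government lists for adjacent districts in the same province are available, geocode those facilities and recompute nearest distance as a second sensitivity analysis. No full facility survey is needed. This should remain a sensitivity analysis, because if women do not cross, in-district distance is the relevant exposure.
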